### Daily Support Messages

#### Overview

All participants will receive daily support messages beginning after the 1-week burn-in period. Each day, participants are sent an SMS text message that will contain a Qualtrics (Qualtrics XM) link. The daily support message is accessed and viewed or read in Qualtrics by clicking on that link. The use of Qualtrics to display the support message allows us to have a time-stamped confirmation that the support message has been accessed that day. Text messages with this Qualtrics link will be sent out at 5 AM each morning in the participant’s own time zone so that the support message is available at the start of the new day upon waking. A reminder is also sent by text message at 11 AM and 4 PM if the participant has not yet accessed the support message in Qualtrics by those times.

The support messages are generated for each participant each night using an LLM (GPT-4o) that is accessed by the STAR system through the Microsoft 365 Copilot application programming interface. LLM prompts and example messages are provided on the OSF repository for this project [80]. The core of each support message is a simple statement that encourages the participant to engage with their recovery that day. In addition to the core statement, the message may include up to 4 additional components of personalized information derived from their linguistic tone or style preferences and the lapse risk prediction model to guide their recovery efforts that day. These components are (1) their current lapse probability for that day and trends in that daily lapse probability over the past 2 weeks, (2) an important lapse feature contributing to their current lapse probability, (3) a risk-relevant recommendation for a recovery activity to complete that day, and (4) linguistic style and tone personalization. These 4 message components are operationalized as follows.

#### Current Lapse Probability and Trends in Daily Lapse Probability Over the Past 2 Weeks

If included, the support message will contain categorical information about the participant’s lapse probability in the next 24 hours based on output from the lapse risk prediction model. Lapse probability will be provided using a 3-level categorization of “low risk” (*P*≤.05), “moderate risk” (.05<*P*≤.20), or “high risk” (*P*>.20). These probability cut points were determined both from clinician input and distributional information in the sample of 151 participants with alcohol use disorder where we developed our model [35]. The cut points represent approximately the 10th and 60th percentiles in the overall distribution of the ~300,000 observed probabilities. The decision to convey lapse probability categorically (rather than numerically) follows current best practice recommendations to avoid complex numerical probability statements, especially for those with low numeracy, and provide the minimal information needed for individuals to assess the magnitude of risk, weigh options, and act [87-91]. It also follows the format from an existing app that characterizes the risk associated with various blood alcohol concentration levels [92].

If included, the support message will also contain categorical information about the trend in the predicted probabilities of a lapse over the past 2 weeks. Lapse probability change will be reported using a 3-level categorization of “decreasing risk” (lapse probability decreases by ≥.05 over 2 weeks), “increasing risk” (probability increases by ≥.05 over 2 weeks), or “stable risk” (probability changes by <.05 over 2 weeks). Lapse probability change is quantified as the difference in mean weekly predicted lapse probability over the 2 previous weeks (ie, week 2 mean–week 1 mean). We use a simple weekly mean difference to capture both linear and more complex (eg, increasing monotonic) trends across these 2 weeks. The 2-week lapse probability trend is provided because trajectory information may make subtle changes in risk level more apparent, can relieve cognitive load associated with monitoring over time, and can provide incremental value beyond absolute risk levels alone [93]. The decision to convey this information categorically follows the same best practice recommendations as for lapse probability [87-92].

#### Important Lapse Feature

If included, the support message will contain a description of 1 important model feature category that contributes to the participant’s predicted lapse probability that day. The feature category will be selected from among the set of important feature categories that day as defined based on the categories’ log-odds values (ie, feature categories that increase or decrease the log-odds of a lapse by >|0.1|). Among this set of important features, features will be ranked or sorted by how often they have been included in recent support messages and then the magnitude of their importance score. This will prioritize providing the participant with information about new but also important risk features. We include this message component because providing risk feature information may help participants both identify which issues to target for change and select appropriate support tools matched to these issues [94]. Emerging best practices from interpretable machine learning suggest that this information may make the machine learning model less of a “black box,” which may build trust, or allow individuals to engage more thoughtfully (eg, questioning false positives and scrutinizing model behavior) and gain insight [95-97].

#### Risk-Relevant Recommendation for a Recovery Activity

If included, the support message will contain a suggestion to consider completing a specific recovery activity that has been identified by the lapse risk prediction model as personally risk-relevant, given their lapse probability and important model features. All recovery activities are drawn from existing empirically based treatment protocols for relapse prevention, including matrix [98], cognitive-behavioral coping skills therapy [99], and motivational enhancement therapy [100]. As with the feature information mentioned earlier, when multiple risk-relevant recovery activities are available and appropriate, given the lapse risk prediction model output, activities that have not been recommended recently will be selected. We include this message component following best practice suggestions to pair risk information with specific action recommendations to address the risk [101]. This component follows directly from the guiding thesis of our research that improved clinical outcomes will result from increases in adaptive, personally relevant engagement rather than simply more engagement. This component also follows recent examples of digital therapeutics that used machine learning prediction models to generate intervention recommendations for medical or health issues other than alcohol use disorder [102,103].

#### Linguistic Style and Tone Personalization

In addition to the relevant lapse risk prediction model–based message components for that participant, the LLM prompt for support message creation also includes details about the linguistic style (formal or informal) and tone (legitimizing, caring and supportive, self-efficacy support, acknowledging, value affirming, and normalizing) for the support message. These styles and tones were selected based on research on linguistic factors that can affect the acceptance and use of advice during algorithmic or computer-mediated communications [44,104], medical decision-making [105-107], and communications more generally [108-111].

At intake, participants rate how much they would like to receive messages written in each of the available tones and styles independently on a 7-point Likert scale with 1=strongly disagree and 7=strongly agree as anchors. Participants are assigned to either receive support messages matched to their preferences (ie, across days, support messages will be written using any of the tones or styles that were rated higher than the neutral midpoint of the scale) or yoked to receive messages that match the preferences of another participant.

### Measures

#### Overview

Detailed descriptions of the measure items, sources, and administration are available on the project’s OSF repository [80]. Our description of study measures is organized into 5 categories: demographic and other stable characteristics, lapse prediction model inputs, primary or optimization outcome, secondary system outcomes, and secondary clinical outcomes. A summary of these measures is also presented in Table 1.

**Table 1 table1:** Measure constructs, sources, frequency, and use.

Constructs	Source	Measurement frequency	Measure use
Geolocation	FollowMee app	Continuous	Model input
Daily experiences and events (eg, craving, affect, stressors, and risky situations)	EMA^a^	Daily	Model input
System engagement	Confirmation support message accessed	Daily	Primary or optimization outcome
Demographics	Laboratory-created	Intake visit	Baseline characterization or covariate
Alcohol use disorder symptoms	*Diagnostic and Statistical Manual of Mental Disorders (Fifth Edition)*	Intake visit	Baseline characterization or covariate
Alcohol use history	Laboratory-created	Intake visit	Baseline characterization or covariate
Lifetime substance use	World Health Organization’s Alcohol, Smoking, and Substance Involvement Screening Test	Intake visit	Baseline characterization or covariate
Trust in automated systems	Adapted from Propensity to Trust Questionnaire and Trust in Automation Scale	Intake visit	Baseline characterization or covariate
Message usefulness	Laboratory-created	8- and 16-week follow-up visits	Secondary system outcome
System trust	Adapted from Trust of Automated Systems Test and Trust in Automation Scale	8- and 16-week follow-up visits	Secondary system outcome
System digital working alliance	Digital Working Alliance Inventory	8- and 16-week follow-up visits	Secondary system outcome
Number of drinking days (past 30 days)	Alcohol Timeline Follow-Back and EMA	8- and 16-week follow-up visits	Secondary clinical outcome
Number of heavy drinking days (past 30 days)	Alcohol Timeline Follow-Back and EMA	8- and 16-week follow-up visits	Secondary clinical outcome
Anxiety	Generalized Anxiety Disorder-7	Intake and 8- and 16-week follow-up visits	Secondary clinical outcome
Depression	Patient Health Questionnaire-9	Intake and 8- and 16-week follow-up visits	Secondary clinical outcome
Human flourishing	Flourishing Measure	Intake and 8- and 16-week follow-up visits	Secondary clinical outcome
Recovery capital	Multidimensional Inventory of Recovery Capital	Intake and 8- and 16-week follow-up visits	Secondary clinical outcome

^a^EMA: ecological momentary assessment.

#### Demographic and Other Baseline Characteristics

At the intake visit, we will collect self-report information about demographics (age, sex at birth, gender identity, sexual orientation, race, ethnicity, household income, education level, marital status, and number of individuals living in the household), *DSM-5* alcohol use disorder symptoms, general alcohol use history characteristics (eg, age of first use, years of regular use, number of quit attempts, and previous treatment received), and lifetime substance use (World Health Organization’s Alcohol, Smoking and Substance Involvement Screening Test [112]). We also measure individual differences in generic trust in automated systems using a subset of items from the Propensity to Trust Questionnaire (6 items [113]) and the Trust in Automation scale (7 items [114]).

#### Lapse Prediction Model Inputs

Input features for the lapse risk prediction model are engineered from two sources: (1) 1 time daily EMA and (2) passively sensed geolocation. Participants will complete 1 brief (less than 1 minute to complete) EMA each day. EMAs will be sent to the participant by SMS text message at 5 PM each night in the participant’s own time zone. These SMS text messages will include a link to a Qualtrics survey optimized for completion on their smartphone. A reminder to complete the survey is sent by text message at 7 PM if a participant has not yet completed it.

On each EMA, participants will report their current mood (ie, affective valence and arousal), their peak alcohol craving since their last EMA, and the occurrence and intensity of any positive events and any stressors or hassles since their last EMA. They also report how likely they are to encounter risky situations (people, places, or things) and pleasant and stressful events in the next week and how confident they are about abstaining from alcohol use in the next week. They conclude each EMA by reporting any alcohol use that they have not yet reported, the time of the start of that use, the duration of the drinking episode, and the number of drinks consumed.

Participants’ location will be continuously sensed passively using the FollowMee (FollowMee LLC) geolocation tracking app. We will increase the predictive signal from geolocation by gathering contextual information about the locations that participants visit frequently (≥2 times per month). For frequent locations, participants will report the location type (eg, home of friend, bar, restaurant, workplace, and Alcoholics Anonymous meeting location), if alcohol is typically present at that location, if they drank there previously, their typical emotional experience at that location (pleasant, unpleasant, mixed, or neutral), and the perceived risk to their recovery associated with that location. This contextual information can be gathered quickly by appending these additional questions about a newly detected frequent location to their next daily EMA.

#### Primary or Optimization Outcome

Our primary outcome for this study is STAR system engagement. System engagement is measured by counting the days that participants access the daily support message by following the link to the support message provided to them by text message. We will calculate message engagement scores that count the number of days the support message is accessed across the full 16 weeks of data collection. Support message engagement serves as the optimization outcome for this study.

#### Secondary System Outcomes

We measure 3 secondary STAR system outcomes at 8 and 16 weeks into the data collection period: daily support message usefulness, system trust, and system digital working alliance. Daily support message usefulness is measured with 7 items scored on a 7-point Likert scale. These items ask participants to rate the perceived helpfulness, general liking, and personal relevance of the messages [115-118]. Trust in the overall STAR recovery monitoring support system is measured with 10 items scored on a 7-point Likert scale. These items come from the Trust of Automated Systems Test (9 items [119]) and the Trust in Automation scale (1 item [114]). The system digital working alliance between the participant and the STAR system is measured with the Digital Working Alliance Inventory [120]. This measure consists of 6 items measured on a 7-point Likert scale.

#### Secondary Clinical Outcomes

We will measure 2 primary clinical outcomes recommended by the Food and Drug Administration [121] for the evaluation of interventions for alcohol use disorder: number of drinking days and number of heavy drinking days in the past 30 days. These 2 outcomes are quantified at 8 and 16 weeks into the data collection period. Information about participant alcohol use is obtained from 2 sources. First, participants report episodes of alcohol use in the daily EMAs as described earlier. Second, study staff conduct a 30-day alcohol Timeline Follow-Back (TLFB) procedure [122] at the study phone visits at 8 and 16 weeks in the data collection period. The TLFB procedure is a calendar-assisted retrospective reconstruction of how many standard alcoholic drinks were consumed by the participant each day in the assessment period. This procedure is further enhanced by adding previously reported drinking episodes (dates, times, and number of drinks) from the daily EMAs to the calendar used with the participant. This provides an opportunity to validate those previous reports and collect any additional drinking episodes that may have been missed by the EMAs. The number of drinking days is defined as the number of days that any alcohol is consumed during the relevant 30-day period. The number of heavy drinking days is defined as the number of days that more than 3 or 4 standard drinks are consumed for women and men, respectively, during the relevant 30-day period. The TLFB will also be administered by study staff during the intake visit to determine inclusion or exclusion criteria (ie, time since last drink).

We will also collect secondary measures of anxiety (General Anxiety Disorder-7 [123]), depression (Patient Health Questionnaire-9 [124]), human flourishing (total score and subscales from the Flourish Measure [125]), and recovery capital (Multidimensional Inventory of Recovery Capital [126]). Each of these measures will be collected at intake and at 8 and 16 weeks into the data collection period.

### Data Analytic Plan

#### Overview

All data preprocessing, visualization, and exploratory analyses will be done using the tidyverse ecosystem [127] in R (R Foundation for Statistical Computing). General or generalized mixed effects models will be fit using the *lme4* package [128] in R. Multiple imputation will be performed using the *mice* package [129].

#### Primary Analyses

MOST [77] highlights the importance of optimizing any intervention prior to evaluating it with a formal randomized controlled trial. The goal of this project is to optimize support message components in the STAR system by identifying which of the several message components increase engagement with the daily support messages. Such information will be crucial to develop future digital therapeutics for alcohol and other substance use disorders that use personalized supportive messages based on machine learning lapse risk prediction models.

Collins [130] advocates for the use of the factorial experiment as a highly efficient and powerful design to optimize intervention components generally. We use this design to evaluate the effects of our 4 message components (current lapse probability and trends in daily lapse probability over the past 2 weeks, important feature contributing to current lapse probability, risk-relevant recommendation for a recovery activity, and linguistic style and tone personalization) on the primary or optimization outcome (count of days of support message engagement) measured at the end of the data collection period (week 16). The goal of these analyses is to determine the effect of each support message component and whether the effect of one component varies depending on the level or setting of another component (eg, Is the effect of a recovery activity recommendation greater if given in combination with lapse probability or an important feature?).

We will analyze support message engagement in a generalized linear model (with Poisson or negative binomial distribution dependent on the distribution diagnostics for the count data). We will use unit-weighted orthogonal contrasts to code for main effects and 2-way interactions among the 4 message components. Support message engagement will be indexed as the count of days on which the support message was accessed by the participant across the full 16 weeks in the data collection period. Baseline covariates will be included in the model, as described in the Covariates section. This analysis will include all participants who were randomized into the study, following intention-to-treat principles. If participants discontinue use of the STAR system during the data collection period, they will get a 0 for each subsequent day they do not engage with the message.

#### Secondary Analyses

Analyses for secondary outcomes will follow the same analytic plan as for the primary analyses but will use the secondary outcomes (eg, daily support message usefulness, system trust, system digital working alliance, and clinical outcomes) as the outcome variable. These analyses will allow us to determine whether the effects of message components on engagement also extend to other perceptions of the STAR system and clinical outcomes. The error distribution (Gaussian, Poisson, and negative binomial) for these generalized linear models will be selected based on the distribution of the outcome variable. These secondary analyses will use mean scores for each outcome across the 16 weeks (ie, average of scores at 8 and 16 weeks) as the dependent measure because the effects of time are not a primary focus, given the relatively short duration of the study. These analyses will only include participants who provided at least 1 measurement for the secondary outcomes during the data collection period (ie, at 8 or 16 weeks). For participants missing 1 measurement, scores will be imputed using multiple imputation (see Missing Data section).

#### Covariates

The use of covariates has been demonstrated to improve estimation efficiency and increase power to test parameter estimates in linear models [131-135]. Given this, the inclusion of baseline characteristics measured prior to assignment to levels for message components will be considered as covariates in the primary and secondary analyses. When available, the baseline scores associated with the study outcome for each model (eg, baseline flourishing for the model examining flourishing) will be included in the model to control for baseline differences on that measure. In addition, following well-established practices in our laboratory [136-138], other baseline characteristics (eg, demographics and alcohol use or history measures and baseline scores on other outcomes) will be included in the model if they demonstrate a significant relationship with the outcome variable for that model, independent of (ie, controlling for) message component effects. This allows for the selection of covariates that will increase statistical power but not bias the parameter estimates for the message component effects.

#### Sample Size Planning

The primary optimization outcome (count of days of support message engagement) will be analyzed in a generalized linear model (with Poisson or negative binomial distribution) and contrast coding for the main effects and 2-way interactions of the 4 message components. We planned the sample size for this study by simulating the power to detect main effects or interactions of the message components across varying effect sizes and baseline (all message components off) support message engagement rates. We simulated count data using the Poisson distribution for support message engagement across 112 days (16 weeks), with λ (mean count for distribution) calculated as the number of days of observation multiplied by the baseline engagement rate. We added a message component effect to these data by increasing the count to reflect an increased rate of support message engagement across days (eg, on 5% more days) when the component was included in the support message. These simulations indicated that 304 participants would provide 85% power to detect a message component main effect or interaction that increased support message engagement rates by 3% of days when the baseline engagement rate was 85% of days. Power was higher still when message effects were larger (ie, >3%) or the baseline engagement rate was lower (eg, <85% of days). We believe that message components that increase engagement rates by less than 3% would not be sufficiently large to warrant including that component in future versions of the STAR system. Furthermore, if baseline engagement exceeds 85%, there would not be much need for support messages to increase engagement further. Therefore, we believed these bounds to be appropriate to represent the minimal clinically meaningful contribution from message components. It should also be noted that this power estimate is likely conservative because it does not include potential covariates that will be included in the analysis model.

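### The stated 85% power holds only if the SD of engagement days is at most about 9.8, and the simulation leaves out the discontinuation that the primary analysis scores as 0

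*Protocol article*

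**What the plan says.** All of this is in the Data Analytic Plan of the protocol article.

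- **Sample Size Planning, method.** "We simulated count data using the Poisson distribution for support message engagement across 112 days (16 weeks"). All simulated participants share one mean; the counts are drawn "with λ (mean count for distribution) calculated as the number of days of observation multiplied by the baseline engagement rate". The component effect is then added to these counts. The section describes no person-to-person variation in the rate and no discontinuation.
- **Sample Size Planning, result.** "These simulations indicated that 304 participants would provide 85% power to detect a message component main effect or interaction". The effect meant here is one which "increased support message engagement rates by 3% of days when the baseline engagement rate was 85% of days".
- **Sample Size Planning, two reassurances.** "Power was higher still when message effects were larger (ie, >3%) or the baseline engagement rate was lower (eg, <85% of days"), and "this power estimate is likely conservative because it does not include potential covariates".
- **Primary Analyses.** "This analysis will include all participants who were randomized into the study, following intention-to-treat principles". For participants who discontinue, "they will get a 0 for each subsequent day they do not engage with the message". The model is Poisson or negative binomial, chosen on diagnostics, so overdispersion is foreseen in the analysis.

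**The concern.** A simulation with one Poisson mean fixes the variance of the outcome at its mean. The analysed outcome is a count between 0 and 112 that includes everyone randomised, with zeros after stopping. A participant who stops halfway scores about half the count of one who continues, so a few such participants widen the distribution considerably. The sample size calculation and the analysis rule therefore describe different outcomes, and the article gives nothing to show that their variances agree. The introduction itself calls falling engagement a known problem in this field.

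The 3% threshold is also the article's own minimum for keeping a component. If the SD is well above the assumed one, a component that truly reaches the threshold would often show no significant effect on the optimization outcome, while the stated power would suggest that this is unlikely.

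**Working it through.** **Inputs from the article.** N=304; 112 days; baseline 85%, so a mean of 0.85 × 112 = 95.2 days; effect 3% of days, so 0.03 × 112 = 3.36 days. **Assumed, because not stated:** two-sided alpha of 0.05; equal allocation (152 with and 152 without each component); stopping times uniform over the 112 days. Only the main effect is checked.

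**Step 1: reproduce the stated figure.** Poisson SD = sqrt(95.2) = 9.76. SE = 9.76 × sqrt(4/304) = 1.119. z = 3.36/1.119 = 3.00. Power = Phi(3.00 − 1.96) = 85.1%. Using the variances of both arms (95.2 and 98.56, average SD 9.84) gives 84.5%. A simulation of the 16-cell Poisson model with four main effects and six two-way interactions gives 85.7%. The 85% is arithmetically right under its own assumption.

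**Step 2: what an SD of 9.8 allows.** If everyone had the same 85% daily rate, the bounded count would have SD sqrt(112 × 0.85 × 0.15) = 3.78, well below 9.76. A between-person SD of 8 percentage points in the rate gives variance 14.28 + 112 × 111 × 0.08² = 93.8, an SD of 9.69. So the Poisson value leaves room for about 8 points of between-person spread, provided that nobody stops.

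**Step 3: power by SD of the count (N=304, effect 3.36 days).** SD 8: 96%; 9.84: 85%; 12: 68%; 15: 50%; 20: 31%; 25: 21%.

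**Step 4: add stopping, with zeros afterwards.** Let a share q stop, and let v be the completer variance (14.28 if binomial, 95.2 if Poisson).

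- Mean = 95.2 × (1 − q/2)
- Variance = (1 − q)(95.2² + v) + q(95.2²/3 + v/2) − mean²
- Power = Phi(effect/(SD × sqrt(4/304)) − 1.96)

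Example with q = 10% and binomial completers: mean 90.44; variance 8169.6 + 302.8 − 8179.4 = 293.0; SD 17.1. The effect is diluted to 3.36 × 0.95 = 3.19 days, so z = 3.19/1.96 = 1.63 and power is 37%.

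| Share stopping | Bounded days, otherwise identical people: SD | Power | Completers with Poisson variance: SD | Power |
|---|---|---|---|---|
| 2% | 8.6 | 92% | 12.4 | about 65% |
| 3% | 10.1 | 81% | 13.5 | 57-58% |
| 5% | 12.6 | 62% | 15.4 | 46-48% |
| 10% | 17.1 | 37% | 19.2 | 30-33% |
| 20% | 22.9 | 21% | 24.5 | 19-22% |

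The bounded column uses the diluted effect. In the Poisson column, the lower figure dilutes the effect and the higher one does not.

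**Step 5: detectable effect at 85% power, Poisson completers.** (1.96 + 1.036) × SD × sqrt(4/304). At 10% stopping this is 6.6 days (5.9% of days); at 20%, 8.4 days (7.5%).

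**Step 6: the covariate argument.** To bring the residual SD back to 9.84, covariates would have to explain 1 − (9.84/15)² = 57% of the variance at SD 15 and 1 − (9.84/20)² = 76% at SD 20. Messages begin only after the burn-in week, so no measure of message engagement exists before randomisation.

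**Step 7: the lower-baseline claim (effect still 3% of days).**

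| Variance model | Power at 85% | at 70% | at 50% |
|---|---|---|---|
| Poisson, no stopping | 84.5% | 90.5% | 97.1% |
| Poisson completers, 10% stopping | 30% | 40% | 62% |
| Bounded, identical people, 10% stopping | 37% | 48% | 71% |
| Bounded, within-person correlation 0.10, no stopping | 65% | 42% | 36% |

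With within-person correlation 0.10 and 10% stopping together, power is roughly flat, between 25% and 28%.

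**The case against.** The strongest defence is that the Poisson variance is not the smallest possible. It is 95.2/14.28 = 6.7 times the binomial variance for a common 85% rate, so it already contains slack. This stands. A reader might infer that the 85% requires every participant to have the same rate. It does not, because about 8 points of between-person spread with no stopping gives nearly the same SD. But stopping alone uses up that slack at about 3%, even when participants are otherwise identical.

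A second defence is that the article gives no SD and no stopping rate, so nobody can say that the trial lacks 85% power. This also stands. With bounded days and identical people, 2% stopping still leaves 92%. The point is that the stated power is conditional, not that it is known to be false.

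Third, a reader might call the lower-baseline sentence a mere Poisson artefact, since Poisson variance falls with the mean. Step 7 does not bear that out. Variance from stopping scales with the squared mean, so power still rises at lower baselines when stopping dominates. It also rises under a negative binomial with constant dispersion, from a much lower level (23% at an 85% baseline and 31% at 70%, with dispersion 0.05). The direction reverses only when between-person variance of a bounded count dominates.

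Fourth, covariates do help in direction. That is correct, but it does not make the figure conservative overall.

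Finally, one might infer that a null result on engagement would discard a useful component. The article would also recommend components that improve clinical outcomes, so that does not follow.

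**Conclusion.** The point holds in conditional form. The 85% power for a 3%-of-days main effect requires an SD of engagement days of at most about 9.8. The calculation has no discontinuation term, while the analysis retains everyone randomised and scores 0 after stopping. Under uniform stopping, about 3% is enough to bring power below the stated level in the most favourable case. At 10% stopping, power is 30-37%, so a component at the article's own threshold would be missed roughly two times in three on engagement.

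The claim that the estimate is probably conservative is not supported, because the omitted between-person and stopping variance can outweigh any covariate gain. The lower-baseline claim is true under some variance models and false under others. This is a problem of assumption, not a calculation error.

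The sizes rest on a two-sided 0.05 test, equal allocation, uniform stopping times and assumed stopping rates. The direction of the stopping effect on the SD does not depend on the particular rates shown.

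**What to change.** Keep N=304. Rerun the simulation with a count bounded at 112 days (for example beta-binomial) plus discontinuation scored 0, over a stated range of within-person correlation and discontinuation. Then restate either the power at 3% of days or the smallest effect detectable with 85% power. Remove or qualify the statement that the estimate is likely conservative, and keep the lower-baseline statement only as far as the rerun supports it.

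The cost is one rerun simulation and a less favourable published figure. No participants, visits or changes to the analysis are needed.
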